### Interim analyses {21b}

No interim analyses have been planned.

### Methods for additional analyses (e.g. subgroup analyses) {20b}

We will carry out exploratory pre-specified analyses to determine whether specific baseline moderators, i.e. (a) caregiver educational level; and (b) social support, modify the intervention’s effect on children’s behavioural problems (CBCL) and caregivers’ quality of life (PEDsQL) at T1 and T2.

We will also assess mediational and post-randomisation moderator effects, which will not be reported in the main trial paper. The mediational analysis will use the interventional in(direct) effects approach [57] that permits simultaneously accounting for post-randomisation moderators and multiple mediators. With it, we can investigate the extent to which the intervention induced change in caregiver quality of life by changing child behavioural problems (our main mediator). The method will also reveal how several indirect effects contributed to the intervention’s total effect. We plan to investigate the following: (i) the indirect effect of the intervention on change in child behavioural problems; (ii) the indirect effects through post-randomisation moderator factors such as the number of CST sessions attended, fidelity of CST group sessions and competence of the CST facilitator, and home practice completed; and (iii) the indirect effects of the intervention through other potential mediators such as social support, caregiver perceived stigma, and physical punishment.

### Methods in analysis to handle protocol non-adherence and any statistical methods to handle missing data {20c}

Our power and sample size calculations account for missing data based on realistic patterns of dropout over repeated measurements. We will produce frequency reports of participants who purposefully withdraw from the trial or are passively lost to follow-up by site and arm at 18 ± 2 weeks post-randomisation (T1) and 44 ± 2 weeks post-randomisation (T2).

We will use intention to treat principles that analyse participants within their randomised clusters, with mixed effects models including participants with at least one outcome measure, assuming data are missing-at-random. Our analyses will also include any baseline variables found to be associated with missing outcome data in models to make the missing-at-random assumption more plausible.

Moreover, if attrition rates exceed the levels assumed in the power calculation, we will compute a sensitivity analysis that will impute missing-data values under two scenarios: (i) outcomes remain unchanged from or return to baseline and (ii) where attrition in the control arm is related to improvement of 0.1 SD and in the active arm is related to a worsening of 0.1 SD [58, 59].

We define adherence as the family participating in at least 7 group sessions and 2 home visits, and if we register non-adherence rates of 10% or more, we will do a complier average causal effect (CACE) analysis for the two primary outcomes [59, 60] as a more principled version of a per-protocol analysis. We will compare those who complied/were adherent in the intervention arm with those in the control arm who would have been adherent if they had been allocated to the intervention arm. The CACE will be obtained using instrumental variable methods [60] with the primary outcome of interest as the dependent variable and adjusting for similar variables to those described for the primary intention to treat analysis. If we later find any individuals were ineligible and mistakenly entered into the trial, we may redo the CACE analysis with these individuals removed.

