### Sample size {14}

Each study cluster comprises 7 to 10 families. In intervention clusters, these families will all participate in the same CST group (with control clusters offered the intervention after data collection has been completed). Following WHO’s recommendations, CST groups will have a maximum of 10 caregivers. We anticipate having higher recruitment rates in the urban areas (i.e. 10 caregivers per cluster) compared to the rural areas (i.e. 7 caregivers per cluster), with an overall anticipated average cluster size of 8.5 caregivers.

Using a simulation and non-central chi-square approach [45], we determined that 14 clusters at each site (*n* = 476 caregivers in total) provided 96% (if effect size = 0.4) and 83% (if effect size = 0.32) power to detect the intervention effect for each co-primary at T1. The method accounted for (1) the cluster design, (2) the two co-primaries using a Bonferroni correction (i.e. alpha = 0.025), (3) realistic patterns of drop-out over repeated measures (i.e. 10% each at post-intervention and follow-up), (4) a missingness at random assumption, (5) pilot-test informed (i.e. 0.4) and conservative effect sizes (i.e. 0.32), and (6) intra-class correlation of 0.05 in our intervention arms. The random effects analysis model also co-varied for baseline and the country/site strata, and allowed for different group random effect variances for intervention and control arms, and different effects at T1 and T2 (i.e. including an intervention arm by time point interaction term in the model, with the effect at T1 extracted as the primary outcome). Furthermore, as this is a psychosocial trial with potential contamination concerns, we increased the number of trial clusters to 16 instead of 14 per site, bringing the total sample size to approximately 544 (i.e. an average of 8.5 families per cluster in 64 clusters) (Table 1).

**Table 1 Tab1:** Ethics approval information from collaborating institutions

Country	Name of ethics committee and/or governing body	Reference number	Status
UK	Health Faculties (purple) Research Ethics Subcommittee-King’s College London	RESCM-23/24–33742	Approved
Ethiopia	Scientific and Ethics Review Committee-Centre for Innovative Development and Therapeutic Trials for Africa (CDT Africa)	CDT/5564/22	Approved
	Institutional Review Board (IRB)-Addis Ababa University College of Health Sciences	AAYMF 03–008	Approved

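### The missing-not-at-random check runs only when attrition exceeds the power-calculation level, and its one numerical shift is mild with no stated reference point

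*Protocol article*

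**What the plan says.** Section {20c} of the protocol article describes "mixed effects models including participants with at least one outcome measure, assuming data are missing-at-random". To support that assumption, the analyses will "include any baseline variables found to be associated with missing outcome data in models to make the missing-at-random assumption more plausible".

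Departures from MAR appear in one sentence of the same section: "if attrition rates exceed the levels assumed in the power calculation, we will compute a sensitivity analysis". Two scenarios follow. The first is "i) outcomes remain unchanged from or return to baseline". In the second, "attrition in the control arm is related to improvement of 0.1 SD and in the active arm is related to a worsening of 0.1 SD".

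The level that sets the trigger is in Sample size {14}: "realistic patterns of drop-out over repeated measures (i.e. 10% each at post-intervention and follow-up". Section {20c} also promises counts of withdrawal and loss to follow-up by site and arm at both time points.

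**The concern.** The attrition rate in a power calculation concerns precision. It does not show whether the people who drop out differ, on the outcome that was not seen, from those who stay. Adding baseline predictors of missingness helps only with dropout that those predictors explain. A trial with 9% attrition can have informative dropout, yet under the stated rule nothing beyond MAR would be examined.

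The trigger is also loosely worded. It does not say whether it applies per arm or to both arms together, nor whether 10% each is per wave or cumulative. Arm-related dropout is plausible here. Control families receive CST only after T2, intervention families are asked to attend nine group sessions and three home visits, participants know their allocation, and both co-primaries are caregiver-reported.

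When the analysis does run, a single shift of 0.1 SD per arm cannot show how large a departure the result would withstand. At stake is whether a significant co-primary result can be described as robust to missing data.

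**Working it through.** **Inputs.** From Sample size {14}: power 96% at 0.4 SD and 83% at 0.32 SD with 14 clusters per site (56 clusters, n = 476); "the two co-primaries using a Bonferroni correction (i.e. alpha = 0.025"; ICC 0.05 in the intervention arm; mean cluster size 8.5; 10% dropout; final size 64 clusters (n = 544). Assumed because not stated: two-sided testing (critical value 2.2414), control-arm ICC 0, baseline–outcome correlation r = 0.3, and equal missingness in the two arms. Effects E are in SD units, positive in favour of CST.

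**1. Reproducing the stated power.** SE = sqrt{(1 − r²) × [(1 + (m′ − 1) × 0.05)/n′ + 1/n′]}, with n′ = 238 × 0.9 = 214.2 per arm and m′ = 8.5 × 0.9 = 7.65. This gives sqrt(0.91 × 2.3325/214.2) = 0.0995, hence power 96.2% and 83.5%, in line with the article.

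**2. SE implied by the plan itself.** 0.40/(2.2414 + 1.7507) = 0.100 and 0.32/(2.2414 + 0.9542) = 0.100, so the two stated powers agree. Scaled to 64 clusters: 0.1001 × sqrt(56/64) = 0.0936. The significance limit is 2.2414 × 0.0936 = 0.210 SD.

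**3. Formulas, with share d missing in each arm.**
- Scenario (ii) as an offset from MAR: E − 0.1 × (d + d) = E − 0.2d.
- Scenario (i), missing values at baseline with arms equal there: (1 − d)E.
- Scenario (ii) as a change from baseline: (1 − d)E − 0.2d.
- Tipping shift per arm (active worse and control better by the same amount): (E − limit)/(2d).

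**4. Results for an observed effect of 0.32 SD.** Tipping A holds the SE at 0.0936. Tipping B and the limit column use the step 1 formula with 272 × (1 − d) per arm, so the SE grows with missingness.

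| Missing per arm | Move under (ii), offset | Tipping A | Tipping B | (ii) offset | (i) | (ii) from baseline | Limit |
|---|---|---|---|---|---|---|---|
| 10% | 0.02 | 0.55 | 0.56 | 0.300 | 0.288 | 0.268 | 0.209 |
| 15% | 0.03 | 0.37 | 0.35 | 0.290 | 0.272 | 0.242 | 0.214 |
| 20% | 0.04 | 0.28 | 0.25 | 0.280 | 0.256 | 0.216 | 0.219 |
| 30% | 0.06 | 0.18 | 0.15 | 0.260 | 0.224 | 0.164 | 0.232 |

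Example for tipping A at 10%: (0.32 − 0.210)/0.20 = 0.55.

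The unstated reference matters. At 20% missing, the same 0.1 SD leaves 0.280 (significant) as an offset from MAR, or 0.216 (just below the limit) as a change from baseline.

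**5. Where the 0.1 SD shift does bite.** As an offset it overturns observed effects of 0.214 to 0.244 SD at 15% missing (0.214 + 0.03) and 0.219 to 0.259 SD at 20% (0.219 + 0.04). With a true effect of 0.32, the chance of such a reversal is about 8% and 12%.

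**6. Where nothing runs.** At exactly 10% missing the trigger is not met. An observed 0.25 SD would be overturned by (0.25 − 0.209)/0.2 ≈ 0.2 SD per arm, and an observed 0.23 SD by about 0.1 SD, the plan's own value. With a true effect of 0.32 and SE 0.093, an observed effect between 0.209 and 0.25 has a chance of about Φ(−0.75) − Φ(−1.19) ≈ 11%.

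**7. Imbalance between arms.** 3% and 16% average 9.5%, which does not meet a pooled trigger. A per-arm trigger would be met by the 16%, but not by, say, 2% versus 9%.

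**The case against.** Several points on the other side stand.

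- Below the trigger, a design-size result is hard to overturn. At 10% missing it takes about 0.55 SD per arm in opposite directions, a contrast of roughly 1.1 SD among dropouts. For 3% versus 16%, (0.32 − 0.210)/0.19 = 0.58 SD per arm. Exposure is confined to results near the limit.
- A per-arm reading of the trigger is open, and loss by arm will be reported in any case.
- Differential dropout is a possibility, not a finding. The baseline caregiver is invited to T1 and T2 whatever their adherence, and the Kenyan pilot reported high retention.
- An analysis plan not shown may add to this. The conditional trigger and the single 0.1 SD value are nonetheless fixed in the protocol text.

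Three stronger readings are tempting, and the document does not support them. A reader might infer that the 0.1 SD shift is too small to change any conclusion; step 5 shows that it can reverse near-limit results. A reader might infer that MAR is never tested. Both scenarios run once the trigger is met, and scenario (i) is the larger departure: at 30% missing it takes 0.32 to 0.224, below the 0.232 limit. That reversal depends on the SE growing with missingness, since with the SE held at 0.0936 the limit is 0.210 and 0.224 stays above it. A reader might also infer that scenario (i) fills in one fixed value per person and so understates the SE. The article says only that values will be imputed, not whether singly or multiply, so no criticism of the SE follows.

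**Conclusion.** The point holds as a limited, inexpensive improvement. The plan fixes a rule under which neither co-primary gets a departure-from-MAR check at or below 10% attrition, and the trigger's unit (per arm or pooled) is undefined. Once triggered, scenario (ii) read as an offset moves the effect by 0.02 to 0.04 SD at 10% to 20% missing, about 0.2 to 0.4 SE. The shift needed to overturn 0.32 SD is about 0.55 to 0.28 SD per arm. Scenario (i) is stronger but equally conditional.

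The figures rest on the stated assumptions: two-sided 0.025, equal missingness except where shown, an SE unchanged by the imputation, and, for the limit column, r = 0.3 and control-arm ICC 0. The tipping shifts change little between the two SE versions. The MAR mixed model as primary analysis is not in question.

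**What to change.** Settle the following before the analysis plan is signed and the trial statistician is unmasked:

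- Run the departure-from-MAR analysis for both co-primaries at T1 and T2 whatever the attrition, overall or by arm.
- State the reference for the SD shift: the MAR prediction or the baseline value.
- After imputation under MAR, vary the shifts in the two arms independently over a range, for example 0 to 0.6 SD worse in the CST arm and 0 to 0.6 SD better in control. That range reaches the tipping point for 0.32 SD at 10% missing (0.55 to 0.56 SD per arm).
- Report the tipping point beside the primary estimate. The return-to-baseline scenario can stay as one of the cases.

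The cost is some wording and a few extra analysis runs, with no new data collection and no change to the primary analysis.

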### Plans to give access to the full protocol, participant-level data, and statistical code {31c}

The full trial protocol and consent forms will be published on the Open Science Framework (OSF) website (https://osf.io/) after the trial protocol paper has been published. Data underlying the results reported in the main trial paper will be made available upon request 12 months after the main trial article has been published. Access to the data will be controlled by the SPARK executive group. Data sharing will be prioritised for teams involving students and researchers in Ethiopia and Kenya in line with the capacity-building aims of the SPARK research programme. We have not yet planned to grant public access to the statistical code.

## Oversight and monitoring

### Composition of the coordinating centre and trial steering committee {5d}

The trial will be supervised and managed by a Trial Management Group (TMG) assisted by country-specific Trial Management Teams (TMTs), a Data Safety and Monitoring Board (DSMB), and a Trial Steering Committee (TSC). The country-specific TMTs will comprise trial staff and will be responsible for country-specific ethics applications, recruiting, training and supervising data collectors, and monitoring the quality of incoming data under the authority and guidance of local coordinating centres and institutions. Their work will be monitored by the cross-country TMG to ensure consistency in procedures. The TMG will include psychiatrists, psychologists, statisticians, epidemiologists, and trial coordinators from Ethiopia, Kenya, and the UK. They will oversee data collection, documentation, management, and the creation of an electronic data capture using REDCap to ensure that high-quality relevant data is collected and retained to protect the participants’ rights.

The DSMB will comprise three members independent of the SPARK study, including clinicians and biostatisticians. The board will meet approximately every 6 months to review data reports from the trial detailing recruitment tallies, cluster randomisation, CST participation and home visit completion rates by cluster and site, progress with data collection and entry at baseline, endpoint, and follow-up time points, and the number and types of SAEs and adverse events (AEs) reported per arm. Based on their review, they will recommend different actions, including pausing or ceasing the trial if irregularities are noted. Masking will be at the board’s discretion, and meetings may be closed or open to observers such as trial representatives.

The TSC will act on the sponsor and funder’s behalf to oversee the project. The committee will include six independent members (i.e. a chair, a statistician, two clinicians, and an informed community stakeholder) and non-independent members like the two project co-PIs, the Ethiopian in-country PI, and the other statisticians. The committee will meet approximately every 6 months, about 2 weeks after the DSMB’s meeting, to review, consider, and decide on recommendations in the DSMB report. Only independent members will have voting rights. Membership in the DSMB and TSC will be mutually exclusive and correspondence between the committees and the SPARK co-PIs will occur through their respective chairs.

### Composition of the data monitoring committee, its role and reporting structure {21a}

See ‘Composition of the coordinating centre and trial steering committee {5d}’ section above.

### Adverse event reporting and harms {22}

We have made provisions for detecting, recording, and managing AEs and SAEs. Adverse events include (i) potential adverse care of the child, including neglect, abuse, and chaining/restraint, (ii) deterioration in physical health or under nutrition of the child, (iii) caregiver suicidal ideation, (iv) stigma and discrimination, and (v) significant change or breakdown in family structure. Serious adverse events include (i) death due to suicide; (ii) death due to any other cause; (iii) suicide attempt; (iv) hospitalisation due to any medical or mental health emergency; (v) violence to others causing injury; and (vi) injury to the caregiver or child from others (life-threatening/requires hospitalisation/causes disability). Research staff may receive information about AEs and SAEs from caregivers, community members, health workers, and data collectors during systematic outcome assessment data collection efforts, trial-related appointment visits with health workers, or through caregiver-initiated reports to the research team outside scheduled visits. Research staff will report all suspected AEs and SAEs to the trial/project coordinator, who will inform the in-country PIs. The in-country PIs will assess the reports for relatedness, seriousness, and expectedness and determine whether the AEs need to be re-categorised as SAEs.

Within 24 h of the research team becoming aware of an SAE, the in-country PI will report the incident to all relevant Institutional Review Boards (IRBs), their internal monitors, and the co-PI at the sponsor institution. The co-PI at the sponsor institution will, in turn, report the incident to the DSMB, sponsor, and ethics committee at the sponsor institution within the same 24-h period of the research team becoming aware of the incident. The in-country-PI will complete and submit the more detailed SAE form within 8 days from the date of awareness to the co-PI at the sponsor institution for authorisation. Within 10 days from the date of awareness, the co-PI at the sponsor institution will submit the authorised SAE form using a secure medium to the DSMB, the sponsor and ethics committee at the sponsor institution, and in-country PI for onward submission to the relevant IRBs and internal monitors. Where the co-PI at the sponsor institution or the in-country PIs are unavailable, delegated staff members will take on these responsibilities.

All AEs and SAEs will be documented on AE/SAE forms and entered in the register of SAEs, which will be managed centrally by the trial coordinator. Tallies of all AEs and SAEs will be included in six-monthly reports to the Data Safety Monitoring Board (DSMB) and Trial Steering Committee (TSC). SAEs will be addressed on a case-by-case basis by members of the DSMB.

Guidelines on how to manage each SAE and AE are detailed in a dedicated standard operating procedure. In brief, all caregivers or children in the intervention and control arms experiencing SAEs/AEs will receive a phone call (for AEs only), visit, or invitation for assessment from CST non-specialist facilitators or research team members (i.e. trial or project coordinators or data collectors). They will be provided with further access to psychosocial or medical assistance based on their needs. Research team members will follow up with the caregiver as needed. Where the SAE/AE hinders a caregiver’s ability to participate in the trial, they will be invited to return, if desired, once the SAE/AE has been sufficiently managed.

### Frequency and plans for auditing trial conduct {23}

We will engage independent country-specific trial monitors with experience in trial monitoring and Good Clinical Practice to review the approved study protocol and conduct at least three site visits for audit purposes. The visits will occur before recruitment begins, at the mid-point, and at the end of the trial.

### Plans for communicating important protocol amendments to relevant parties (e.g. trial participants, ethical committees) {25}

The trial management group and site-specific trial management teams will communicate all important protocol modifications to relevant parties such as the interventionists, investigators, ethics committees/IRBs, trial participants, monitoring committee members, trial registries, and journals.

### Dissemination plans {31a}

We will prepare different kinds of outputs to communicate the trial’s results to researchers and stakeholders such as representative organisations for people with DD and their caregivers, policymakers, representatives from national and international non-governmental organisations, members of our national and community advisory boards, media representatives, and the public. Examples of the types of outputs we will prepare include peer-reviewed manuscripts, oral and poster presentations, flyers, toolkits, theory of change maps, policy briefs, and press releases.

All outputs will be made available on the SPARK website (https://www.thesparkproject.net/). In addition, we will organise specific events like social science cafes and project and community advisory board meetings to discuss these outputs and directly engage with stakeholders. We will use a targeted approach in developing and distributing the outputs to ensure stakeholders receive them in preferred formats and at an opportune time to increase the chances of uptake.

## Discussion

The WHO CST programme has previously been adapted and pilot-tested in field trials in 30 + countries [7]. The findings from these early studies suggest that it may be an acceptable, feasible, and effective intervention for children with DDs such as autism and intellectual disability and their caregivers. However, these investigations have been limited by several factors such as small sample sizes, delivery by specialists instead of non-specialist facilitators, a focus on autistic children only, and limited implementation in LMICs [17, 19, 21]. This study addresses these gaps through the conduct of a well-powered large trial and the generation of evidence of the effectiveness of the non-specialist-delivered version of CST in improving the mental health and well-being of children with DDs and their caregivers in two LMICs. The trial will also help to determine the resource impacts and costs and consequences associated with the intervention. This project aligns with the recently published WHO UNICEF Global report on children with developmental disabilities, which called for action to strengthen services, address stigmatisation, and inform, empower, and support caregivers of children with DD [1].

Despite the trial’s importance and potential positive impact, there are some ethical concerns to consider. First, participating in this trial may expose the child’s condition to community members, potentially increasing the risk of experiencing stigma and discrimination. We have minimised this risk by employing community sensitisation efforts in each of the trial areas, raising awareness of DDs, addressing negative beliefs about children with DDs in the community, and training staff in the importance of maintaining confidentiality. In addition, all trial workers received training in how to address stigma when it occurs and how to minimise the risk of stigma by ensuring participant confidentiality at all times. Secondly, participation in the CST programme may raise caregivers’ hopes for a cure for their child’s condition that cannot be met in this trial and are unrealistic given the chronic nature of their children’s conditions. The information sheet and consent process explicitly address this expectation of a cure, and this topic is also addressed during CST group sessions.

The WHO CST intervention targets children aged 2–9 years with developmental delays in the social-communicative domain. Our trial recruits participants through community identification. There will be children identified in the community needing support who do not meet the trial’s inclusion criteria (e.g. because they fall outside the target age) or meet one or more of the trial’s exclusion criteria (e.g. co-occurring severe motor impairments). Our trial is conducted in a context where support systems for these children may not be fully developed. To mitigate this ethical concern, we have ensured local health and/or education workers in each cluster are trained in principles of the WHO mhGAP developmental disorder module, which constitutes enhanced care as usual since this training is not typically available in Ethiopian and Kenyan communities. Moreover, we have developed site-specific resource kits describing relevant support services available in each community to assist families with relevant referrals.

This trial seeks to test the effectiveness of the WHO’s CST as delivered by non-specialist facilitators at improving the mental health and wellbeing of children with DD and their caregivers living in four sites across Kenya and Ethiopia, in contexts where formal support for these families is largely unavailable, and families are impacted by poverty, stigma, and social exclusion. The project will also test the resource impacts and costs and consequences of the intervention. The findings of this trial can inform future implementation and scale-up of intervention services for families with children with developmental disabilities in Kenya and Ethiopia, as well as inform implementation in other low-resource contexts.

